## Abstract

**Background::**

Minimal hepatic encephalopathy (MHE) is a subclinical state of hepatic encephalopathy with the possibility of developing into overt hepatic encephalopathy (OHE) and having adverse outcomes. However, no preventative medicine for MHE has been recommended so far. The aim is to evaluate the therapeutic effect of the *JianPi HuaZhuo XingNao* formula (*JPHZXN*) on MHE, specifically whether *JPHZXN* decreases OHE occurrence, through a randomized controlled trial.

**Method::**

Seventy-two patients with MHE are enrolled and allocated in a 1:1 ratio in an experimental group and a control group. *JPHZXN* granules and placebos are dispatched to the experimental group and control group, respectively, for 24 weeks. The primary outcome is the incidence of developing OHE. The secondary outcomes are the patients’ performances in number connection test A and the digital sign test as well as results from the health survey and chronic liver disease questionnaire.

**Results::**

This study will provide proof regarding the therapeutic effect of *JPHZXN* among patients with MHE.

**Conclusion::**

The outcomes could grant clinicians an alternative choice when treating potentially progressive patients with MHE.

## Introduction

1

### Background

1.1

Minimal hepatic encephalopathy (MHE) is a unique disease stage of covert hepatic encephalopathy (CHE), and it is one of the complications caused by liver dysfunction.^[1]^ As it is in a subclinical state, it is difficult to identify, and it has no apparent psychologic or neurologic clinical manifestation. However, symptoms can be detected through sophisticated neuropsychologic and neurophysiologic tests.^[2]^ MHE debases patients’ quality of life by, for example, restricting their abilities to drive and work, and it is highly possible that MHE will further develop into overt hepatic encephalopathy (OHE).^[3]^ Therefore, MHE poses a significant potential hazard to individuals and society.^[4]^ Thus, it is significant to diagnose MHE and CHE and to prevent MHE from progressing to OHE. According to epidemiologic surveys, MHE or CHE occurs in 20% to 80% of patients with cirrhosiss.^[5–8]^ Therapies including lactulose, lactitol, probiotics, and rifaximin have been applied in the treatment and research of MHE, and they have shown the effect of preventing OHE from the first attack.^[9,10]^ However, none of these therapies is adequate for recommendation as a routine or preventive treatment. According to the 2014 Practice Guideline by the American Association for the Study of Liver Diseases, routine or preventive medicine is not recommended for MHE.^[11]^ The medical community lacks a clear consensus regarding how to treat the disease.

Liver cirrhosis is the most critical cause of hepatic decompensation, and chronic hepatitis B (CHB) is a principal cause of cirrhosis in China, which is a mid-high endemic region.^[12]^ The cure for hepatic encephalopathy, as an essential complication of cirrhosis, shall be systematic and multidimensional. The treatment for CHB is as necessary as the treatment for MHE itself. The *JianPi HuaZhuo XingNao* (*JPHZXN*) formula adopted in this research was refined from therapeutic drugs for CHB used in former studies (the *Shuanghu qinggan* granule and *Yigan yiqi jieyu* granule),^[13]^ having a defined effect for both the treatment of CHB and hepatic encephalopathy. In the situation with the lack of agreement regarding the treatment of MHE, the use of the *JPHZXN* formula with high-risk patients suffering from MHE that originated from CHB-induced cirrhosis can restrict primary diseases and reduce the possibility of OHE attacks. Moreover, the therapy avoids overtreatment by combining CHB and MHE therapies into a single formula of traditional Chinese medicine.

### Objectives

1.2

#### Primary objective

1.2.1

The primary objective is to determine whether the *JPHZXN* formula could decrease the occurrence of OHE among patients with MHE.

#### Secondary objectives

1.2.2

The secondary objectives are to determine whether the *JPHZXN* formula could improve the performance in number connection test A (NCT-A) and the digital sign test (DST) as well as the quality of life of patients with MHE (evaluated by the Medical Outcomes Study item short-form health survey—36 items [SF-36] and chronic liver disease questionnaire [CLDQ]).

### Trial design

1.3

We designed this trial as a double-blinded, randomized, and controlled exploratory trial. We will implement simple randomization with a 1:1 allocation ratio in 72 eligible patients. The primary endpoint is the occurrence of OHE within 24 weeks.

## Methods: recruitment, interventions, and outcomes

2

### Study setting

2.1

Seventy-two patients from the clinic and inpatient department of the Dongzhimen Hospital affiliated to Beijing University of Chinese Medicine, Beijing, are recruited for this pilot study.

### Criteria

2.2

All patients should provide a signed informed consent form before enrollment.

#### Inclusion criteria

2.2.1

Participants should meet all the following criteria:

1.Be diagnosed with CHB, referring to the guideline of prevention and treatment for CHB (2015 version)^[14]^2.Be diagnosed with hepatocirrhosis through a liver ultrasound, computed tomography scan, magnetic resonance imaging, or other imaging examination or show histologic evidence of hepatocirrhosis (including stage 4 liver fibrosis)3.Be diagnosed with MHE through neurophysiology and neuropsychology tests4.Be voluntary participants in this project after signing the informed consent form

#### Exclusion criteria

2.2.2

Participants who meet any of the following criteria should not be enrolled:

1.Are aged under 18 or over 752.Have ruled out HBV infection as the primary cause of the hepatocirrhosis3.Have severe complications of hepatocirrhosis (electrolyte disorders, gastrointestinal bleeding, infections)4.Have been diagnosed with a mental illness or cerebrovascular disease5.Have taken a sedative in the last 4 weeks6.Have been long-term drinkers for at least 5 years (equivalent to 40 g of ethanol per day for males or 20 g/d for females) or heavy drinkers (equivalent to 40 g of ethanol per day) within 2 weeks.7.Have body temperatures over 37.5°C8.Have cardiovascular, pulmonary, renal, endocrine, nerve, and hematology diseases9.Have been diagnosed with a malignant tumor10.Cannot cooperate with this research due to other reasons

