#### Trial drugs

2.4.1

Both groups will be treated with trial drugs for 24 weeks. The experimental group will receive 1 dose per day of the *JPHZXN* formula, whereas the control group will be given the *JPHZXN* formula placebo. The real drugs and placebos are consistent in shape, color, and taste.

The patients will be allowed to continue their basic treatment for hepatocirrhosis and CHB. In addition to receiving the trial drugs for MHE (Detailed in *2.4.4 Relevant interventions*).

The major ingredients of the *JPHZXN* formula are listed in Table 1.

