##### Rescue medicine

2.4.3.1

Patients who progress from MHE to OHE during the trial will leave the trial cohort and be given standard treatment. They will be given 15 to 30 mL of oral lactulose per dose, with 2 to 3 doses per day. If the condition persists without remission, probiotics and rifaximin will be prescribed. The principles of diagnosis and treatment for OHE abide by the instructions from the American Association for the Study of Liver Diseases.^[11]^

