##### Basic treatment in addition to the trial drug

2.4.4.1

Antiviral, antifibrosis, and liver protection therapies are allowed during the course (Table 2), but medications that directly affect blood ammonia or could improve cognitive performance (such as lactulose, lactitol, probiotics, and rifaximin) are prohibited until observable OHE.

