### Outcomes

2.5

The primary therapeutic outcome is the incidence measure of OHE within 24 weeks. An OHE attack is defined an adverse outcome.

The secondary outcomes are the results of the NCT-A, DST, SF-36, and CLDQ. The NCT-A and DST will be applied to measure patients’ neuropsychology performances, and an extended completion time will indicate cognition impairments.^[15,16]^ The SF-36^[17]^ and CLDQ^[18]^ are regular measurements of life quality among patients with hepatocirrhosis, and reduced scores for these tests designate impaired life quality.

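### Drugs prohibited during the trial (such as lactulose or rifaximin) have no look-back at entry, so a current user can be enrolled and would then have to stop

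*Protocol article*

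**What the plan says.** Section 2.4.4.1 sets the rule during treatment: "medications that directly affect blood ammonia or could improve cognitive performance (such as lactulose, lactitol, probiotics, and rifaximin) are prohibited until observable OHE".

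Section 2.2.1 lists four inclusion criteria and section 2.2.2 lists ten exclusion criteria. Two exclusions carry a recent-exposure window: "Have taken a sedative in the last 4 weeks", and, for alcohol, "heavy drinkers (equivalent to 40 g of ethanol per day) within 2 weeks". No criterion mentions current or recent use of the drugs prohibited in 2.4.4.1, and the printed text describes no washout or run-in.

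On background therapy, section 2.4.1 says: "The patients will be allowed to continue their basic treatment for hepatocirrhosis and CHB". Section 2.4.4.1 then takes the ammonia-lowering and cognition-improving drugs out of what may be used.

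On the relevance of these drugs, section 1.1 says that "they have shown the effect of preventing OHE from the first attack", although it adds that none is recommended for routine or preventive use. Section 2.4.3.1 makes lactulose the first treatment once OHE has occurred: "They will be given 15 to 30 mL of oral lactulose per dose". The primary outcome, in section 2.5, is OHE itself: "The primary therapeutic outcome is the incidence measure of OHE within 24 weeks".

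**The concern.** The entry rules and the conduct rules do not meet. A drug class that matters enough to be banned during the trial is not asked about at entry, while sedatives and alcohol are. A patient already on lactulose or rifaximin therefore passes every listed criterion and comes under the prohibition on joining.

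Three things follow:

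- **Patient risk.** The patient would have to give up a drug that the authors describe as protective against the very event being counted, and may be allocated to placebo.
- **Baseline.** The MHE diagnosis and the baseline number connection test A (NCT-A) and digital sign test (DST) could be measured on drug and so not describe the patient under trial conditions.
- **Primary outcome.** An OHE that follows stopping would enter the count with no means of telling it apart from natural progression.

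**Working it through.** The core of the check is a comparison of sections.

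1. *Is the drug class barred during the trial?* Yes, by 2.4.4.1, until OHE is observed.
2. *Does any inclusion criterion screen out current users?* No. The four items in 2.2.1 cover hepatitis B, cirrhosis, MHE and consent. The MHE item asks for neurophysiological and neuropsychological testing and sets no off-drug condition.
3. *Does any exclusion criterion do so?* No. Of the ten items in 2.2.2, the sedative item (4 weeks) is the one drug look-back, and heavy drinking (2 weeks) is the other short exposure window. Item 10 is a general exclusion for inability to cooperate. It names no drug or period, and a patient willing to stop lactulose is cooperating.
4. *Could the drug continue as background therapy?* No. The permission in 2.4.1 is general, and 2.4.4.1 specifically removes this class.
5. *Result.* A current user is eligible and, to comply, must stop. No section orders withdrawal in those words; it follows from the prohibition.

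**Size of the patient risk.** The plan gives no figure to reproduce. The total of 72 (36 + 36) comes from section 2.7. The number of users K and the rise r in 24-week OHE risk from stopping are assumptions, because the documents give neither.

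Extra OHE events over both arms = K × r.

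| Users K (share of 72) | r = 0.05 | r = 0.10 | r = 0.20 |
|---|---|---|---|
| 7 (7/72 = 10%) | 0.35 | 0.70 | 1.40 |
| 14 (14/72 = 19%) | 0.70 | 1.40 | 2.80 |
| 22 (22/72 = 31%) | 1.10 | 2.20 | 4.40 |

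If K is near zero, so is every entry.

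**Precision of the cognitive outcomes.** No figure is given. An on-drug baseline followed by off-drug results would add noise to a change from baseline, but 2.5 defines the secondary outcomes as the test results and 4.3 names *t* or Wilcoxon rank-sum tests without saying that changes are analysed. If follow-up values are compared, the baseline mismatch adds none.

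**The case against.** The strongest reply is that this is a condensed article. Prior-medication handling and screening steps may be in the full protocol, and Figure 1 (the assessment schedule) and Table 2 (the permitted basic treatments) are not shown. A run-in, or the timing of the baseline tests, could appear in Figure 1. This stands as a limit: the statement about baseline is that it *could* be on drug. It does not remove the point, because the article prints a numbered exclusion list that reads as complete and includes windows for other exposures. Eligibility is also not something a protocol leaves to an analysis plan.

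A second reply is that experienced physicians supervise recruitment (2.3) and could refuse such a patient under item 10. They could, but that leaves the decision to individual judgement and does not reach a patient who agrees to stop. Consent, visits every 4 weeks (4.1) and lactulose once OHE occurs limit the harm without preventing it.

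A third reply is that use may be rare, since 1.1 reports that routine or preventive medicine is not recommended for MHE and that the condition is hard to identify. This stands, and it keeps the point small.

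A reader might also infer stronger claims that the documents do not support:

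- *The comparison between arms is biased.* Allocation is random, so prior use is balanced in expectation. Chance imbalance with 36 per arm is possible but is not systematic bias.
- *The trial loses precision on NCT-A and DST.* That needs a change-from-baseline analysis, which is not stated.
- *Section 2.4.1 by itself forbids all other treatment.* It grants a permission; the restriction comes from 2.4.4.1.

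**Conclusion.** The point holds as a gap between the entry criteria and the concomitant-drug rule. Followed as written, the plan admits a patient on lactulose, lactitol, probiotics or rifaximin and then obliges that patient to stop, although section 1.1 says these drugs have shown an effect against a first OHE attack. What is at stake is avoidable risk to those patients, and an MHE diagnosis and baseline that may describe a treated state.

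The size is uncertain and may be small. The range of 0.35 to 4.4 extra OHE events over both arms rests entirely on assumed values for the share of users and the effect of stopping. The safety argument does not need those values, since it applies to even one such patient. The conclusion also assumes that no washout is set in material not shown. This is a cheap improvement that the sponsor could make, not a flaw that threatens the trial's conclusions.

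**What to change.** Add one exclusion to 2.2.2, for example: *Have taken lactulose, lactitol, probiotics, rifaximin or any other drug prohibited in 2.4.4.1 in the last 4 weeks.* The 4 weeks mirrors the sedative item, and the length should be confirmed clinically. Add one sentence stating that no patient is to be taken off a needed drug in order to qualify. With the exclusion in place, an MHE diagnosis and baseline NCT-A and DST done at entry would be off drug.

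The cost is two sentences and a slightly smaller eligible pool.

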### Research personnel

2.3

Experienced physicians (attending physicians, with a minimum 5 years of clinical experience in the department of hepatology or gastroenterology) will be responsible for supervising the recruitments and performing host interviews and physical examinations. Postgraduate students who majored in hepatology will be trained by the principal investigator before participating in the study. They will dispatch drugs, fill in case report forms, and input electronic case report forms.

### Interventions

2.4

#### Trial drugs

2.4.1

Both groups will be treated with trial drugs for 24 weeks. The experimental group will receive 1 dose per day of the *JPHZXN* formula, whereas the control group will be given the *JPHZXN* formula placebo. The real drugs and placebos are consistent in shape, color, and taste.

The patients will be allowed to continue their basic treatment for hepatocirrhosis and CHB. In addition to receiving the trial drugs for MHE (Detailed in *2.4.4 Relevant interventions*).

The major ingredients of the *JPHZXN* formula are listed in Table 1.

**Table 1 T1:**
[figure not shown]
The major ingredients of JPHZXN granule.

#### Placebos

2.4.2

The corresponding placebos are composed of a mixture of 5% primary formula (trial medicine) with 95% secondary formula (including 0.3% caramel pigment, 0.02% sunset yellow 87, 0.02% tartrazine 85, and 99.66% dextrin).

#### Criteria for modifying interventions

2.4.3

##### Rescue medicine

2.4.3.1

Patients who progress from MHE to OHE during the trial will leave the trial cohort and be given standard treatment. They will be given 15 to 30 mL of oral lactulose per dose, with 2 to 3 doses per day. If the condition persists without remission, probiotics and rifaximin will be prescribed. The principles of diagnosis and treatment for OHE abide by the instructions from the American Association for the Study of Liver Diseases.^[11]^

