### Interviews

4.1

Patients will be interviewed every 4 weeks after enrollment in the clinic, where they should return the used packages and remaining drugs. Adequate trial drugs for 28 days will be dispatched during each interview. A series of tests will be conducted in different weeks (Fig. 1).

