### Statistical methods

4.3

We will carry out efficacy analyses with the full analysis set, which will include those who provided baseline data and at least one post-treatment assessment. Safety analyses will assess all of the randomly assigned patients.

We will apply a chi-square test to compare the occurrence of OHE attacks among groups.

We will assess the secondary outcomes with the Shapiro–Wilk test. We will assess the normally distributed data with *t* tests. We will assess data that were not normally distributed with nonparametric Wilcoxon rank-sum testing.

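### Patients leave the cohort at OHE, the primary endpoint, so their later NCT-A, DST, SF-36 and CLDQ values are not collected and observed end-of-treatment scores come from a selected group

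*Protocol article*

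**What the plan says.** All references are to the protocol article.

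- **Primary objective (1.2.1):** to "determine whether the *JPHZXN* formula could decrease the occurrence of OHE among patients with MHE".
- **Outcomes (2.5):** "The primary therapeutic outcome is the incidence measure of OHE within 24 weeks". In the same section: "The secondary outcomes are the results of the NCT-A, DST, SF-36, and CLDQ". Longer completion times mean worse cognition, and lower questionnaire scores mean worse quality of life.
- **Trial drugs (2.4.1):** "Both groups will be treated with trial drugs for 24 weeks". Section 4.1 sets clinic visits every 4 weeks and leaves the weeks of the individual tests to Figure 1, which is not shown.
- **Rescue medicine (2.4.3.1):** "Patients who progress from MHE to OHE during the trial will leave the trial cohort and be given standard treatment".
- **Statistical methods (4.3):** efficacy is analysed on the "full analysis set, which will include those who provided baseline data and at least one post-treatment assessment". Normally distributed secondary data get t tests. Otherwise: "We will assess data that were not normally distributed with nonparametric Wilcoxon rank-sum testing".

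No section provides for cognitive or quality-of-life testing after OHE, or says how a patient who progressed enters the secondary comparisons.

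**The concern.** The event that ends a patient's participation is the event that the treatment is meant to change. The arms are comparable at randomisation, but the patients still under observation at the end of treatment need not be. If patients with worse scores are likelier to progress, an effective formula keeps more of them in its own arm, while the control arm loses them. The remaining control patients then look better than the control arm as randomised. A formula that raises OHE gains from the same mechanism.

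The four secondary outcomes are the trial's only cognitive and quality-of-life evidence (1.2.2). A real benefit on them could be masked, or could seem to disagree with the primary result, through selection alone. The exit rule governs data collection, so no later analysis choice can supply assessments that were never made.

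**Working it through.** **No planned figure to reproduce.** Section 2.7 sets 36 per group (2 × 36 = 72) without an event rate or effect size, and says that OHE incidence in MHE is inadequately known. All rates and strengths of association below are assumptions. Scores are in SD units with higher meaning worse (questionnaires reversed), and the drug has no effect on the score itself.

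**Check 1: logistic model.** Severity X is N(0,1), and logit P(OHE) = a + bX, with a set to give each arm's assumed OHE rate. The mean severity of retained patients is E[X(1 − P)] / E[1 − P]. The bias is this mean on the formula minus the mean in control. If the score correlates r with X, the bias is multiplied by r.

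| Slope b | 30% v 15%, r = 1 | 30% v 15%, r = 0.7 | 30% v 10%, r = 1 | 30% v 10%, r = 0.7 |
|---|---|---|---|---|
| 0.5 | 0.070 | 0.05 | 0.094 | 0.07 |
| 1 | 0.120 | 0.08 | 0.162 | 0.11 |
| 1.5 | 0.152 | 0.11 | 0.205 | 0.14 |
| 2 | 0.171 | 0.12 | 0.232 | 0.16 |

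Example (b = 1, 30% v 15%): the retained means are −0.253 in control and −0.133 on the formula, so the bias is −0.133 − (−0.253) = 0.120 SD against the formula. The whole table runs from 0.05 to 0.23 SD. Rates of 20% v 10% with r = 1 and slopes 1 to 2 give 0.08 to 0.12 SD.

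**Check 2: latent-normal model.** The score correlates rho with OHE liability, and OHE occurs in the worst fraction p of each arm. The mean of retained patients is −rho × φ(z₁₋ₚ)/(1 − p).

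At 30% v 15%, φ(z)/(1 − p) is 0.3477/0.70 = 0.497 in control and 0.2332/0.85 = 0.274 on the formula. With rho = 0.5 the bias is 0.5 × (0.497 − 0.274) = 0.11 SD. Simulation with 36 per arm and 20,000 replicates gave 0.113.

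With control OHE of 20% to 50%, halved by treatment:

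| rho | Bias (SD) | Two-sided type I error, nominal 5% | Power for a true 0.5 SD benefit, non-progressors only |
|---|---|---|---|
| 0.3 | 0.05 to 0.11 | 5.3% to 6.5% | 42% to 25% |
| 0.5 | 0.08 to 0.19 | 5.6% to 9.6% | 40% to 19% |
| 0.7 | 0.11 to 0.26 | 7.4% to 16.3% | 38% to 14% |

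With all 36 per arm followed, power for the same benefit is about 55%. The loss has two sources: fewer patients and the bias.

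**Scale.** At 30% v 15% the expected non-progressors are 36 × 0.70 = 25.2 and 36 × 0.85 = 30.6. The standard error of the difference is √(1/25.2 + 1/30.6) = 0.27 SD. The check 1 biases at these rates, 0.05 to 0.17 SD, are about 0.2 to 0.6 of one standard error.

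**When it vanishes.** In both models the bias is zero if the arms have equal OHE rates, or if OHE risk is unrelated to the score (b = 0 or rho = 0).

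**The case against.** **The text does not limit the comparison to week 24 or to non-progressors.** This stands. A reader might infer that week-24 scores are compared only among patients who did not progress. Week 24 is an inference from the treatment period. The full analysis set keeps a progressor who had an earlier post-treatment assessment, and whether that value is carried forward, ranked or left missing is not stated. What remains is narrower: such a patient has no observed end-of-treatment value, and a value carried forward would predate the OHE.

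**Handling of OHE in the secondary analysis is SAP material.** Partly right. A SAP could choose a composite or worst-rank approach using only the OHE date. It could not recover scores lost under the stated exit rule.

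**The size may be small.** Fair. The upper figures treat the score as identical to the severity that drives OHE. If OHE risk depended only on the measured baseline score, baseline adjustment would remove the bias. The stated t and rank-sum tests mention no such adjustment, and it would not suffice if OHE followed deterioration during the trial.

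**Safety.** A reader might infer that adverse-event recording stops at OHE and so is shorter in the arm with more OHE. The documents do not say so. Section 5.2 has progressive OHE needing intensive care reported to the committees, and section 4.3 covers all randomised patients. Only routine recording after exit is left unclear.

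**Consequence.** These are secondary outcomes in a self-described exploratory pilot. That limits the weight of the point but does not remove it.

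**Conclusion.** The point holds in limited form. As written, the exit rule stops collection of NCT-A, DST, SF-36 and CLDQ at an event that treatment is expected to influence, so randomisation no longer protects a comparison of observed end-of-treatment scores. The direction is against a formula that prevents OHE and in favour of one that raises it, provided that worse scores go with higher OHE risk.

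Roughly 0.05 to 0.23 SD is an illustration that rests on assumed rates of 30% v 10% to 15% and assumed links between score and OHE risk. The documents cannot narrow it. They do not support the stronger prediction that a working formula will look harmful on cognition: at 30% v 15% the bias is well under one standard error. The exit rule does not affect the primary OHE comparison, because progressors are counted as events. The change should be made, but the trial's main result does not depend on it.

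**What to change.** 1. **Section 2.4.3.1.** Reword so that at OHE patients leave study treatment but stay in follow-up. Record the scheduled NCT-A, DST, SF-36 and CLDQ (where feasible), adverse events and vital status to week 24. The provisions for treating OHE stay as they are.
2. **Section 4.3.** Compare the secondary outcomes on all randomised patients regardless of OHE. Add, as a sensitivity analysis, a rank-sum comparison in which OHE or death takes the worst rank. Label the non-progressor comparison descriptive.

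Worst rank should not be the main analysis, because it puts the primary event into all four secondary outcomes, which would then partly retest the primary.

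**Cost.** Wording in two sections, and continued use of the existing 4-weekly visits for patients who progress. Scores after OHE will include the effect of standard OHE treatment, and some patients may be untestable, so some values will still be missing.
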